# High-precision stereotactic irradiation for focal drug-resistant epilepsy versus standard treatment: a randomized waitlist-controlled trial (the PRECISION trial)

**DOI:** 10.1186/s13063-024-08168-9

**Published:** 2024-05-21

**Keywords:** Epilepsy, Radiosurgery, Stereotactic radiation therapy (SRT), MRI, Cognition

## Abstract

**Introduction:**

The standard treatment for patients with focal drug-resistant epilepsy (DRE) who are not eligible for open brain surgery is the continuation of anti-seizure medication (ASM) and neuromodulation. This treatment does not cure epilepsy but only decreases severity. The PRECISION trial offers a non-invasive, possibly curative intervention for these patients, which consist of a single stereotactic radiotherapy (SRT) treatment. Previous studies have shown promising results of SRT in this patient population. Nevertheless, this intervention is not yet available and reimbursed in the Netherlands. We hypothesize that: SRT is a superior treatment option compared to palliative standard of care, for patients with focal DRE, not eligible for open surgery, resulting in a higher reduction of seizure frequency (with 50% of the patients reaching a 75% seizure frequency reduction at 2 years follow-up).

**Methods:**

In this waitlist-controlled phase 3 clinical trial, participants are randomly assigned in a 1:1 ratio to either receive SRT as the intervention, while the standard treatments consist of ASM continuation and neuromodulation. After 2-year follow-up, patients randomized for the standard treatment (waitlist-control group) are offered SRT. Patients aged ≥ 18 years with focal DRE and a pretreatment defined epileptogenic zone (EZ) not eligible for open surgery will be included. The intervention is a LINAC-based single fraction (24 Gy) SRT treatment. The target volume is defined as the epileptogenic zone (EZ) on all (non) invasive examinations. The seizure frequency will be monitored on a daily basis using an electronic diary and an automatic seizure detection system during the night. Potential side effects are evaluated using advanced MRI, cognitive evaluation, Common Toxicity Criteria, and patient-reported outcome questionnaires. In addition, the cost-effectiveness of the SRT treatment will be evaluated.

**Discussion:**

This is the first randomized trial comparing SRT with standard of care in patients with DRE, non-eligible for open surgery. The primary objective is to determine whether SRT significantly reduces the seizure frequency 2 years after treatment. The results of this trial can influence the current clinical practice and medical cost reimbursement in the Netherlands for patients with focal DRE who are not eligible for open surgery, providing a non-invasive curative treatment option.

**Trial registration:**

Clinicaltrials.gov Identifier: NCT05182437. Registered on September 27, 2021.

**Supplementary Information:**

The online version contains supplementary material available at 10.1186/s13063-024-08168-9.

## Background

Epilepsy has an incidence of around ~ 200,000 patients in the Netherlands and is a great burden to many patients due to the unpredictability of the seizures, a low quality of life, and the increased mortality rate in patients with epilepsy [1–4]. The population of interest for this trial is the group of patients with chronic and focal (= localization related) drug-resistant epilepsy (DRE) who are not eligible for, or do not want to undergo, open resective surgery. In the Netherlands, patients are selected for epilepsy surgery after discussion in a multidisciplinary team in three regional epilepsy surgery working groups connected to three university hospitals (UMC Utrecht, Amsterdam UMC, Maastricht UMC +) resulting in a total of approximately 200–250 surgeries per year [5]. The postoperative seizure freedom rates (= curation) vary between 60 and 90% with epileptogenic lesions on MRI and lesion type as major predictive factors [6]. It is estimated that about 140–150 patients/year within the Netherlands with a suspected focal origin of seizures cannot be offered open surgery and will receive the indication for palliative treatment (deep brain or vagus nerve stimulation (DBS or VNS) and chronic anti-seizure medication (ASM). Seizures and chronic use of ASM cause different somatic and mental side effects and bring also psychosocial consequences, e.g., feelings of dependence, anxiety, depression, and stigma, each impacting patients’ quality of life. Furthermore, the associated yearly healthcare costs for society are expected to be more than the 2004 estimate of €9500 per patient [7–9].

In the PRECISION trial, adult patients with focal DRE, not eligible for surgery, are offered non-invasive linear accelerator (LINAC)-based stereotactic radiotherapy (SRT) with curative intent. SRT has been used to treat several types of neoplasms in the brain for several decades. LINAC-based SRT refers to delivering the dose in one or several treatment sessions. SRT has been proven safe and effective for high-precision radiation treatment of small target volumes, e.g., brain metastases, benign tumors such as meningioma, pituitary adenoma, and vestibular schwannoma, in particular for those locations not easily accessible for surgery [10, 11].

Several publications (level 2 evidence) have shown the potential value of SRT in patients with DRE [12–16]; however, no level 1 evidence was provided enabling guideline development. The systematic review of Eekers et al. has shown that SRT resulted in a significant seizure cure or reduction in 58% of the 170 included patients, within 2 years after treatment [17]. However, all the evidence from the studies described in the review are from cohort studies with a relative low number of patients, who had different pathological lesions as a cause for their epilepsy. In addition, the radiotherapy treatment schedules were diverse (Fig. 1). Interestingly, the ROSE trial, randomizing between open surgery and SRT, has demonstrated a seizure remission of 52% in the radiotherapy group after 2 years with the proportion of seizure-free patients still increasing with a longer follow-up up to 74% after 3 years [4]. At the moment, there is neither a randomized study available comparing seizure outcome after SRT with the current standard of care treatment for this population nor a cost-effectiveness analysis. Therefore, the current trial is necessary to show the relative (cost-)effectiveness of SRT in comparison to the standard care for patient’s ineligible for surgery.

**Fig. 1 Fig1:**
[figure not shown]
Adapted from Eekers et al. [17]. Summarizing the percentage of patients with a radiotherapy-adapted Engel class (RAEC) I or II. On the horizontal axis, the study numbers are given; on the vertical axis, the post-treatment RAEC outcome percentage of patients is plotted. The numbers given and the size of the respective bubble indicate the number of patients included in each study. The green color indicates a single fraction, while red highlights multiple fractions. The prescribed dose (number of fractions times the mean fraction dose) is given above each bubble. * = the ROSE trial [6]

The primary objective of this phase 3 randomized waitlist-controlled trial is to determine whether stereotactic radiotherapy (SRT) reduces the seizure frequency resulting in a reduction of at least 75% (radiotherapy-adapted Engel classification (RAEC) I–III [17]) 2 years after treatment in patients with focal DRE and not eligible for open surgery, when compared to standard of care. Secondary objectives are to assess quality of life (QoL) and neuro-cognition after SRT, (serious) adverse effects, and ASM use and to investigate the cost-effectiveness of SRT compared to standard of care.

## Methods/design

### Study design

Patients will be included for the superiority randomized waitlist-controlled PRECISION trial in the department of radiation oncology (Maastro), Maastricht, the Netherlands. Patients will be randomized in a 1:1 ratio between SRT and current standard care (waitlist-control group), where the latter includes ASM and neuromodulation (i.e., DBS or VNS). The waitlist-controlled group will be offered SRT after the follow-up period of 2 years (optional), if the patients still meet the inclusion and exclusion criteria (Fig. 2). We hypothesize that SRT is a (cost)effective method to alter the epileptogenic cerebral tissue to yield a reduction in seizures and possibly cure after 2 years, with a significant increase in the patients’ quality of life [7, 10].

**Fig. 2 Fig2:**
[figure not shown]
Schematic overview of the study design (RT, radiotherapy; ASM, anti-seizure medication)

### Sample size calculation

Participants will be randomized between SRT and standard of care at a ratio of 1:1. We expect that 50% of the patients in the SRT group will reach RAEC I–III after 2-year follow-up compared to at best 15% in the standard of care group [17, 18]. Sample size calculation is based on a two-sided *Z*-test for proportions with pooled variance and continuity correction. Significance level alpha is set at 0.05 and power at 0.90. Dropout is set at 10%. A total number of 84 patients is needed for the analysis, randomized equally to the SRT group and the standard of care group. After correction for drop-out, the total number of patients becomes 94, with 47 patients randomized to each treatment arm.

### Recruitment

In the Netherlands, there are 3 multidisciplinary comprehensive epilepsy-surgery conference groups, in 3 different regions. The neurologists of the 3 conference groups were informed by the researchers about the PRECISION trial, and each group has a contact person for PRECISION. The neurologists can find more details of the PRECISION trial (e.g., in- exclusion criteria) on the website of Maastro. Potential patients from all conference groups will be evaluated by the multidisciplinary comprehensive epilepsy surgery conference of Maastricht UMC + and Kempenhaeghe (AWEC), consisting of inter alia, a neurologist, neurosurgeon, radiologist, neuropsychologist, and a radiation oncologist, for eligibility. In case the patient meets the inclusion criteria, the treating physician will ask the patients' permission to be contacted by Maastro. Informed consent and recruitment will be performed by the radiation-oncologists from Maastro. The recruitment period of the trial is 3.5 years, with an estimated accrual rate of 2–3 patients per month.

### Inclusion and exclusion criteria

Patients with focal DRE not eligible for surgery are eligible for this study. In addition, all patients must meet all the following criteria:Age ≥ 18 yearsWritten informed consent is given according to International Conference on Harmonization Good Clinical Practice (ICH-GCP) and national/local regulationsThe patient is willing to use contraception during the SRT treatment and for at least 30 days following the SRT therapyThe patient or caretaker is able to keep an epilepsy diaryThe patient has a diagnosis of epilepsy established by a dedicated neurologistThe patient had at least 3 focal-onset seizures over a 3-month period despite two or more antiseizure medication trials (according ILAE Task Force on therapeutic strategies)Video electroencephalography and work-up in the multidisciplinary team to determine a well-circumscribed seizure focus is availableThere is evidence (e.g., 3 T-MRI or a clear SEEG delineation) of the anatomic region to be targeted with SRT, correlating with the seizure focus;A functional MRI to lateralize language or localize visual, motor, and/or sensory eloquent cortex has been performed in selected patients (if the lesion is expected to be located, based on anatomy, in eloquent areas)The patient has completed a standard battery of neuropsychological testingThe patient been deemed an appropriate candidate for stereotactic radiosurgery by a dedicated radiotherapist, neurosurgeon, and epileptologist and referred for the study by one of the Dutch regional multidisciplinary epilepsy surgery working groupsPatients that were rejected for surgery in an earlier stage can participate in the trial if the last change of the VNS/DBS settings were more than 1 year ago or VNS/DBS was not (yet) tried.

The most important exclusion criteria are as follows: pregnancy, prior cranial radiotherapy, or a clinically significant and uncontrolled major other medical condition(s). In addition, if a radiation treatment plan without exceeding the constraints for the organs at risk is not feasible, patients will be excluded from this study.

### Study treatment

Patients in the intervention arm will receive LINAC-based stereotactic radiotherapy (SRT). The target volume is defined as the epileptogenic zone (EZ) on all clinically available (non) invasive examinations in combination with the dedicated MRI and planning CT images acquired within the trial. A single fraction SRT is given with a prescribed isotoxic dose of 24 Gy to the 100% surrounding isodose. Dose is depending on the proximity and maximum tolerable dose to the radiosensitive organs at risk, the EZ volume, and location (e.g., eloquent areas) resulting in a V12Gy ≤ 10.9 cc reducing the risk on radiation necrosis [19]. Therefore, the standard prescription dose will be 24 Gy but can be lowered to 18 Gy based on the V12Gy.

The waitlist-control group (= comparator) will be composed as follows. In case a patient is rejected for open epilepsy surgery and randomized to the waitlist, he/she will receive a proposal for palliative treatment options, i.a. vagal nerve stimulation (VNS) or deep brain stimulation (DBS), as there are currently no other curative treatment options available in the Netherlands. In case the patient rejects these invasive palliative treatment options, continuation of ASM therapy is the only actual option. After follow-up period of 2 years, this waitlist-control group is offered the SRT treatment (optional) if they still meet the inclusion and exclusion criteria.

### Comparison to current standard treatment

#### Comparison to anti-seizure medication (ASM)

According to the Dutch Epilepsy guidelines from the Dutch Neurology Society (NVN), the standard of care treatment for patients with focal epilepsy is ASM. In patients with drug-resistant epilepsy, 10% become seizure free following ASM adjustment, and an additional 10% have a greater than 75% improvement in seizure control after a median follow-up of 4 years [18].

#### Comparison to neuromodulation

VNS and DBS are both palliative treatment alternatives when patients are not eligible for open surgery. In a setting of shared decision-making with the patients rejected for open surgery, both VNS and DBS are offered as treatment alternatives. In general, VNS efficacy becomes optimal around the sixth month of treatment, and response rates (percentage of patients with at least 50% seizure frequency reduction) are achieved in approximately 45 to 65% of the patients [20], with 4% seizure freedom in adult patients with drug-resistant epilepsy [21]. These percentages are similar for the DBS patients. Compared to 55–70% seizure freedom rates 5–10 years after resective or disconnective surgery, neuromodulation is considered a palliative treatment.

### Use of co-intervention

Both in the study as well as in the waitlist-controlled arm, patients should continue their ASM. In accordance with clinical practice, the use of ASM will be considered for reduction and/or stopped after a seizure free period of at least 12 months. A specific co-intervention is not applicable. The risk of developing symptomatic edema or seizures following stereotactic radiosurgery (SRS) is poorly defined, and practitioners can prescribe corticosteroids and/or additional ASM. Therefore, we administer prescribe dexamethasone four days from start SRT, with a dose of 8–6–4–2 mg on consecutive days in patients with symptoms [22].

### Study procedures

Patients which are randomized for the intervention arm will receive SRT, which requires the preparation for radiation treatment. This includes imaging (MRI/CT), preparation of the immobilization devices, radiotherapy treatment planning, and the delivery of a single fraction SRT with a prescribed isotoxic dose of 24 Gy to the epileptogenic zone.

For all patients, the study procedures (Table 1) include the following.

**Table 1 Tab1:** Study procedures

**Time point**	**Minimal follow-up**			**Prolonged follow-up**		
	**Pre-SRT**	**1 year**	**2 years**	**3 years**	**4 years**	**5 years**
Informed consent	X					
Epilepsy consultation - Seizure frequency - Seizure type - Seizure-free days - RAEC	X	X	X	X	X	X
Epilepsy - Nightly epilepsy seizure detection device (Nightwatch) - Epilepsy diary (Helpilepsy)	Continuous					
Quality of life questionnaires	X	X	X	X	X	X
Cost-effectiveness questionnaires	X	X	X	X	X	X
MR imaging	X		X		^a^	
Cognitive evaluation	X		X		^a^	
Visual field examination (only if SRT is in visual tract)	X		X		^a^	

^a^Waitlist-control group: patients which choose SRT will have additional 2-year follow-up including MRI and neurocognitive assessment

#### Epileptic seizure evaluation

Continuously, epilepsy diary information will be collected with the aid of a mobile phone application (Helpilepsy, Overijse, Belgium [23]). In addition, a nightly epilepsy seizure detection device (Nightwatch, Leiden, the Netherlands [24]) will be provided to the patients with the aim to detect eventual nocturnal seizures. The Nightwatch measurements are connected to the Helpilepsy application to provide the patient and the research team a total data capture of events. Patients are asked to annotate the type of experienced seizure. A monthly data extraction will be performed. In addition, on an annual basis, a follow-up consultation is scheduled with the trial assistant to evaluate the post-treatment severity of epilepsy and determine the RAEC.

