#### Visual examination

Visual field examination will only be performed if the (to be treated) EZ is in the proximity of the visual pathway.

If there is missing information (e.g., missed appointments, questionnaires or diary information), the trial assistant will contact the patient.

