### Study parameters and endpoints

The main study endpoint of this study is the reduction of seizure frequency in patients with focal DRE, resulting in a higher proportion of patients who show an improvement of at least 75% (radiotherapy-adapted Engel classification I–III) at 2 years. Secondary study endpoints are to assess the quality of life (QoL) after SRT, define safety, evaluate (serious) adverse effects, ASM use, and tolerability of SRT, and investigate the cost-effectiveness (CEA) of SRT compared to standard of care, neurocognitive, and MR imaging changes after treatment.

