### Statistical analysis

Analysis for the primary endpoint will be based on the intention-to-treat principle. Comparison between the SRT and standard of care group will be performed with a two-sided *Z*-test for proportions with significance level alpha 0.05. For this purpose, the proportion of patients reaching RAEC I–III per treatment group will be calculated and compared. Furthermore, the difference in proportions between groups will be determined and presented with the corresponding 95% confidence interval.

Statistical analysis for secondary endpoints will depend on the type of data and comparison. Differences between treatment and waitlist-control group are central to the analysis and will be presented as effect size and 95% confidence intervals. For categorical data, comparisons will be made using chi-square tests. Data from continuous variables will be checked for Gaussian distribution. Comparison of continuous variables of Gaussian-distributed groups will be performed using the independent samples *t*-test; for non-parametric analyses, the Mann–Whitney test will be adopted.

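### The class that decides the primary test is set at a yearly consultation by an assistant not described as blinded, and the article does not tie it to the diary and detector record

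*Protocol article*

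**What the plan says.** All references are to the Protocol article.

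- **Endpoint.** Study parameters and endpoints sets the target as a "higher proportion of patients who show an improvement of at least 75% (radiotherapy-adapted Engel classification I–III) at 2 years".
- **Test.** Under Statistical analysis, "the proportion of patients reaching RAEC I–III per treatment group will be calculated and compared" by a two-sided Z-test, by intention to treat.
- **How RAEC is obtained.** Epileptic seizure evaluation states that "on an annual basis, a follow-up consultation is scheduled with the trial assistant to evaluate the post-treatment severity of epilepsy and determine the RAEC". The sentence is introduced as an addition to the diary, the detector and the monthly extraction.
- **Table 1 (Study procedures).** One row reads "Epilepsy consultation - Seizure frequency - Seizure type - Seizure-free days - RAEC" and is ticked before treatment and yearly. The diary and night detector have a separate row marked as continuous.
- **The prospective record.** "Continuously, epilepsy diary information will be collected with the aid of a mobile phone application", and "The Nightwatch measurements are connected to the Helpilepsy application to provide the patient and the research team a total data capture of events". The Abstract adds: "The seizure frequency will be monitored on a daily basis using an electronic diary and an automatic seizure detection system during the night".
- **Gaps.** The section on Visual examination ends: "If there is missing information (e.g., missed appointments, questionnaires or diary information), the trial assistant will contact the patient".

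**The concern.** The trial turns on a yes/no status at a 75% cut in seizure frequency. The article describes a prospective record well suited to that classification. It then assigns the classification to a yearly consultation without saying which data are used there, over which baseline and follow-up periods, or what happens if the consultation and the diary disagree. One arm is irradiated and the other waits, so patients know their allocation. The person who determines the class is not described as blinded.

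Two kinds of error are possible. Misreading that is equal in both arms raises the low control rate more than it changes a rate near 50%, so it narrows the difference and costs power. A more generous reading in the radiotherapy arm would push the result towards superiority whether or not there is an effect.

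**Working it through.** **Step 1: reproduce the plan's own figure.** Inputs from Sample size calculation: 50% v 15%, two-sided alpha 0.05, power 0.90, pooled variance, continuity correction, 10% dropout. The mean rate is 0.325 and the difference 0.35.

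- Uncorrected n per arm = [1.96 × √(2 × 0.325 × 0.675) + 1.2816 × √(0.5 × 0.5 + 0.15 × 0.85)]² / 0.35² = (1.298 + 0.787)² / 0.1225 = 35.5.
- Corrected n per arm = (35.5/4) × [1 + √(1 + 4/(35.5 × 0.35))]² = 41.02, rounded up to 42, so 84 in total.
- Dropout: 84/0.9 = 93.3, rounded up to 94, or 47 per arm.

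The stated 84 and 94 are correct, and this point changes no input to them.

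**Step 2: set the statements side by side.**

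| Question | What the article states |
|---|---|
| What is tested? | RAEC I–III proportion |
| Who sets RAEC, and when? | Trial assistant, yearly consultation |
| Is that person blinded? | Not described |
| What is recorded prospectively? | Diary and linked night detector, extracted monthly |
| Is RAEC derived from that record? | Not stated |
| Baseline and 2-year counting periods? | Not stated |
| Which source prevails if they differ? | Not stated |

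**Step 3: illustrate what classification error could do.** The error rates below are assumptions; the article gives none. The calculations enumerate exact binomial probabilities with 42 per arm. Statistical analysis names the Z-test without repeating the continuity correction, so both versions are shown.

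(a) Equal error e in both directions and both arms, with true rates of 50% and 15%. Observed rate = p(1 − e) + (1 − p)e. The 50% rate stays at 50%. The control rate becomes 0.15 × 0.95 + 0.85 × 0.05 = 18.5% at e = 5%, and 0.15 × 0.90 + 0.85 × 0.10 = 22% at e = 10%.

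| e | Control rate seen | Power, corrected | Power, plain |
|---|---|---|---|
| 0 | 15% | 0.910 | 0.946 |
| 5% | 18.5% | 0.824 | 0.881 |
| 10% | 22% | 0.709 | 0.786 |

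(b) No true effect (15% in both arms), with a share f of radiotherapy non-responders recorded as responders. Observed radiotherapy rate = 0.15 + 0.85f. The nominal chance of a false claim in this direction is 2.5%.

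| f | Radiotherapy rate seen | False claim, corrected | False claim, plain |
|---|---|---|---|
| 0 | 15% | 1.0% | 2.7% |
| 5% | 19.25% | 3.6% | 7.7% |
| 10% | 23.5% | 9.7% | 16.9% |

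(c) A milder version of (a): only patients near the cut are at risk. If 20% to 30% of patients lie near it and 10% of those are misread, overall error is 2% to 3%. The control rate seen is then 16.4% to 17.1%, and power is 0.88 to 0.86 with the corrected test or 0.92 to 0.91 with the plain test.

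**The case against.** The strongest reply is that the diary is plainly the intended source. The Abstract says seizure frequency is monitored by diary and detector, and the endpoint is a reduction in seizure frequency. Ability to keep a diary is an inclusion criterion. The RAEC sentence closes the paragraph that describes the diary and its extraction, and the assistant who determines RAEC also follows up missing diary information. Separate rows in Table 1 may reflect only separate schedules. The article is condensed, a full protocol exists (Data Availability), and RAEC itself is defined in a cited review that is not shown.

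Much of this stands. A reader might infer that recalled seizure counts will decide the trial. The documents do not support that: they say who determines RAEC and when, not that it rests on memory. A reader might also infer that missed diary days are filled in later from recall. The text says only that the patient is contacted.

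The size of the effect is also open to challenge. Scenarios (a) and (b) apply the error to whole response classes, although patients who are seizure-free or unchanged are unlikely to be misread. They also treat the diary as free of error. Scenario (c) shows a smaller loss under a milder assumption.

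What remains is that the article is not silent on how the primary class is obtained. It names the consultation, and none of the sentences pointing to the diary mentions RAEC. For a primary outcome in a trial where patients know their arm, the source should not have to be inferred.

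**Conclusion.** The point holds as an unsettled measurement rule, not as a numerical error. The class behind the primary test has one stated origin: a yearly consultation with an assistant not described as blinded. Nothing in the article requires that assistant to use the prospective record, although the text suggests that this was the intention. An arm-blind derivation from data already being collected is less open to bias.

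The power and false-claim figures illustrate sensitivity under assumed error rates; they are not properties of the plan. Under equal error they run from a small loss (0.91 to 0.88, corrected test, 2% error) to a substantial one (0.71 at 10%). The sponsor should make the change, but the article gives no evidence that misclassification of any given size will occur.

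**What to change.** State in Epileptic seizure evaluation, Study parameters and endpoints and Statistical analysis that:

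1. The 2-year RAEC I–III status is derived from the monthly-extracted diary counts and confirmed detector counts.
2. It compares a pre-specified follow-up window with a pre-specified baseline period.
3. The derivation follows a pre-written rule applied without the arm label.
4. The RAEC determined at the consultation is reported as a sensitivity result.
5. Diary days completed after the assistant's contact are flagged, and their exclusion is examined in a sensitivity analysis only, because leaving them out could itself be informative.

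The cost is wording plus a programmed rule on data already extracted; no visit is added. There are three downsides. A minimum diary-coverage rule is needed. No pre-randomisation diary period is stated, so the baseline may have to come from the pre-treatment consultation. Patients who know their arm still make the entries, so bias is reduced but not removed.

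Recruitment began on 1 December 2023 (Trial status), so the first 2-year assessments fall due from about December 2025. The rule should be fixed before any outcome is examined by arm.
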